### Monitoring

Quality assurance will be based on a central and on-site monitoring. The central monitoring encompasses monitoring of data entry progress. Trial sites will also be regularly visited by independent monitors. Visits will focus on controlling regulatory compliance, monitoring of processes, and verification of data that cannot be monitored centrally.

### Data management

In the Preserve-Transplant study, all data will be entered electronically using an internet-based secure data base (secuTrial®) developed in agreement with the Good Clinical Practice (GCP) guidelines. Data integrity is enforced through a variety of mechanisms. Regular backup of the data is assured.

### Statistical analysis

The analysis population consists of all patients who were randomized and have valid data for baseline and at least one follow-up. The primary and secondary endpoints will be analyzed with linear mixed models. Moreover, exploratory subgroup analyses are planned with respect to baseline eGFR to evaluate whether subgroups with lower baseline eGFR will show a better response to alkali treatment compared to subgroups with higher baseline eGFR. Any further details will be specified in the statistical analysis plan.

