### Objectives and hypothesis

The primary objective of PTS is to test if alkali treatment will preserve kidney graft function and diminish the progression of chronic kidney disease in renal transplant patients by assesing the change in eGFR over 2 years from baseline compared to placebo.

Additionally we want to investigate underlying pathomechanisms of metabolic acidosis and how metabolic acidosis may promote disease progression. A further objective is to identify reliable candidate biomarkers that would allow selecting specific transplant patients that may benefit from alkali therapy.

This study assesses long-term safety of the study drug with a particular focus on new onset and worsening of hypertension, volume overload, and gastrointestinal side effects. Selected adverse events (AEs) and all serious adverse events (SAEs) will be documented regularly and compared between the treatment and placebo group.

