### Study population

Kidney transplant patients will be recruited from all study centers according to the inclusion and exclusion criteria (Table 2).

**Table 2 Tab2:** Inclusion and Exclusion Criteria of the Preserve-Transplant Study

Inclusion Criteria	
• Informed consent as documented by signature	
• Age ≥ 18 years and able to give informed consent	
• ≥ 12 months after renal transplantation	
• Stable clinical condition	
• Stable graft function over the last 6 months (creatinine changes ±15%)	
• eGFR between 15 and 89 ml/min/1.73 m^2^	
• At least one serum bicarbonate measured ≤22 mmol/l within the last 6 months	
Exclusion Criteria	
• Uncontrolled hypertension or use of > 4 antihypertensive agents	
• Uncontrolled heart failure	
• Serum potassium < 3.0 mmol/l	
• Serum sodium > 150 mmol/l	
• Use of alkali in the preceding 4 weeks	
• Use of mineralocorticoid antagonists, topiramate, carbo anhydrase inhibitors or any drugs with similar effects	
• History of noncompliance with clinic visits	
• Hereditary fructose intolerance	
• Known hypersensitivity or allergy to the drug used in this study or to peanut, sorbitol, and soy	
• Pregnancy or breastfeeding	
• Intention to become pregnant during the course of the study	
• Lack of safe contraception, defined as: Female participants of childbearing potential, not using and not willing to continue using a medically reliable method of contraception for the entire study duration, such as oral, injectable, or implantable contraceptives, or intrauterine contraceptive devices, or who are not using any other method considered sufficiently reliable by the investigator in individual cases. Please note that female participants who are surgically sterilised / hysterectomised or post-menopausal for longer than 2 years are not considered as being of child bearing potential.	
• Suspected drug or alcohol abuse	
• Inability to follow the procedures of the study, e.g. due to language problems, psychological disorders, dementia, etc. of the participant	
• Enrolment of the investigator, his/her family members, employees and other dependent persons	

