### Sample size

Based on a retrospective analysis of our own cohort, it was assumed that the mean annual eGFR decline in the placebo group will be 1.5 ml/min/1.73 m^2^ and that this decline can be reduced to 0 ml/min/1.73 m^2^ in the treatment group as a result of alkali therapy based on previously published data for CKD patients with metabolic acidosis. Power was determined on the basis of a two-sided, two-sample t-test of the slopes over 2 years. Group sizes of 150 will achieve 82% power to find a minimum detectable difference in the mean slope over 2 years of − 3.0 with estimated group standard deviations of 9.0 and with a significance level of 0.05 using a two-sided two-sample t-test. Therefore, a total number of 300 patients for the entire study is planned.

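### The question whether lower baseline eGFR goes with a better response would be answered more efficiently by a continuous treatment-by-eGFR interaction than by subgroups

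*Protocol article*

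**What the plan says.** All statements are in the protocol article.

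- **Statistical analysis, the model:** "The primary and secondary endpoints will be analyzed with linear mixed models".
- **Statistical analysis, the subgroup plan:** "exploratory subgroup analyses are planned with respect to baseline eGFR to evaluate whether subgroups with lower baseline eGFR will show a better response", and this is "compared to subgroups with higher baseline eGFR". The number of groups, the cut-points and the test are not given.
- **Statistical analysis, the rest:** "Any further details will be specified in the statistical analysis plan".
- **Study population, Table 2:** the entry criterion is "eGFR between 15 and 89 ml/min/1.73 m^2", so the modifier is continuous over a wide range. Its expected distribution is not given.
- **Sample size:** "Group sizes of 150 will achieve 82% power" for a two-year difference of "3.0 with estimated group standard deviations of 9.0", at a two-sided 0.05 level.

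**The concern.** The question is whether the effect of alkali varies with baseline eGFR. Every patient has a baseline eGFR value, and the planned mixed model can carry a treatment-by-baseline-eGFR term. Grouping replaces that value with a category and so discards the variation within each category. A trial sized for a main effect has little power for effect modification to begin with, so a loss that can be avoided is worth avoiding.

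A second hazard is conditional. If subgroup results were read side by side, each by its own p-value, a pattern such as benefit only at low eGFR could easily arise when the true effect is the same throughout. The Discussion hopes that the results will inform treatment recommendations, so such a pattern might be given more weight than an exploratory result deserves.

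**Working it through.** **Inputs.** From the Sample size section: 150 per arm, difference 3.0, SD 9.0, two-sided 0.05. From Table 2: baseline eGFR 15 to 89. Assumed here: no dropout, a t-test on the two-year change standing in for the mixed model, the same SD in every subgroup, a linear gradient for the information loss, and several possible eGFR distributions (normal, uniform on 15–89, and normal truncated to 15–89 with mean/SD 45/15, 50/18 and 55/18).

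**1. The plan's own figure.** SE of the main effect = 9 × √(2/150) = 1.04. Power = Φ(3.0/1.04 − 1.96) = 82.3%, or 82.1% with the noncentral t. The stated 82% is reproduced.

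**2. Information lost by grouping.** For a linear gradient, the share of information kept equals the squared correlation between baseline eGFR and its group score. For a median split this is 2/π = 0.64 with a normal baseline (36% lost) and 0.75 with a uniform baseline (25% lost).

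| Grouping | Loss across the assumed distributions |
|---|---|
| Median split | 25–36% |
| Tertiles | 11–21% |
| Quartiles | 6–15% |
| Four groups cut at 30, 45, 60 | 9–13% |
| Lowest third against the rest | 33–41% |
| Lowest quarter against the rest | 43–47% |
| Two groups cut at 30 | 52–72% |

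The rows with cut-points at fixed eGFR values use the uniform and truncated normal distributions only.

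**3. Power for effect modification.** With equal halves there are 75 per arm in each. The SE within a half is 9 × √(2/75) = 1.47, and the SE of the difference between halves is √2 × 1.47 = 2.08. For 80% power the halves must differ by (1.96 + 0.84) × 2.08 = 5.8, almost twice the planned main effect. The power of the continuous term follows by dividing z for the split by √0.64 (normal) or √0.75 (uniform).

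| True gap between halves | z for the split | Power, median split | Power, continuous (uniform to normal baseline) |
|---|---|---|---|
| 3.0 | 3.0/2.08 = 1.44 | 30% | 38–44% |
| 4.0 | 4.0/2.08 = 1.92 | 49% | 60–67% |

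**4. Discordance if subgroups are tested separately.** Suppose the true effect is 3.0 everywhere. A half with 75 per arm has power 0.527. The chance that exactly one of two halves is significant is 2 × 0.527 × 0.473 = 0.50. For k equal groups, each with power P, the chance that some but not all are significant is 1 − P^k − (1 − P)^k. This gives 71% for three groups (50 per arm, P = 0.379) and 74% for four (37 per arm, P = 0.293). A direct interaction test at 0.05 would declare different effects in only 5% of such trials.

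**The case against.** The strongest objection is that the figures depend on choices the article does not make. It does not say that eGFR is split in two, at the median or elsewhere. It does not say that each subgroup is judged by its own p-value. Its comparative wording can mean a direct contrast between subgroups, and interaction tests are commonly reported under the name of subgroup analysis. Details go to an analysis plan that is not shown, so missing cut-points or an unnamed test are no fault of a condensed article. The analysis is labelled exploratory, and no confirmatory claim hangs on it. The continuous term also has a price: if benefit has a threshold, groups may describe it better.

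Most of this stands, and it rules out three stronger readings that a reader might infer.

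- **That this plan discards a fixed share of the information, such as a quarter to a third.** That size belongs to a median split with a linear gradient. The table above runs from 6% to 72%, and the article fixes neither the grouping nor the eGFR distribution.
- **That the plan will often produce discordant subgroups by chance.** This follows only from separate tests, which the article neither prescribes nor excludes.
- **That the same fault affects the objective to "identify reliable candidate biomarkers that would allow selecting specific transplant patients that may benefit from alkali therapy".** The Objectives and hypothesis section names no method for it, so there is no choice of method to criticise.

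What the objection does not remove is that the article names grouping as its approach to a continuous modifier. Every grouping examined loses information under a linear gradient, even when the groups are contrasted directly.

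**Conclusion.** The point holds as a minor improvement to an exploratory analysis. It does not touch the primary result. For a roughly linear gradient, grouping costs about 25–36% of the interaction information with a median split and about 6–21% with tertiles or quartiles, and more with an uneven two-way cut. In power, a gap of 4.0 between halves would be detected 49% of the time with a median split and 60–67% of the time with continuous eGFR. Even the better method is underpowered for a gap as large as the planned main effect (38–44% at 3.0), so neither version can settle the question.

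The 50% discordance between two halves is a warning about one way of reading subgroups. It is not a property of the plan as written. All loss and power figures rest on assumed eGFR distributions, no dropout, and an SD of 9.0 in every subgroup.

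**What to change.** State in the analysis plan that the main exploratory analysis of effect modification is one treatment-by-baseline-eGFR interaction on the two-year eGFR change, with baseline eGFR continuous, within the planned linear mixed model. If the model is written in terms of slopes, this is the treatment-by-baseline-eGFR-by-time term, with its lower-order terms included. Report the interaction with its confidence interval and the estimated treatment effect at several eGFR values, for example 30, 45 and 60. Keep subgroup estimates as description only, with no separate significance statement for each.

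The cost is one model term and a sentence of wording; no further patients, visits or data are needed. The downside is the assumption of a roughly linear gradient. A spline can check it, but with limited power at 300 patients, and a threshold effect might be better seen in the descriptive subgroup estimates.

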### Sample size

Based on a retrospective analysis of our own cohort, it was assumed that the mean annual eGFR decline in the placebo group will be 1.5 ml/min/1.73 m^2^ and that this decline can be reduced to 0 ml/min/1.73 m^2^ in the treatment group as a result of alkali therapy based on previously published data for CKD patients with metabolic acidosis. Power was determined on the basis of a two-sided, two-sample t-test of the slopes over 2 years. Group sizes of 150 will achieve 82% power to find a minimum detectable difference in the mean slope over 2 years of − 3.0 with estimated group standard deviations of 9.0 and with a significance level of 0.05 using a two-sided two-sample t-test. Therefore, a total number of 300 patients for the entire study is planned.

## Discussion

Metabolic acidosis is a serious complication in patients with CKD with deleterious effects on kidney function and patient survival. A recent retrospective study has evidenced that MA is also associated with increased risk of graft loss and patient mortality in kidney transplant recipients [19]. Although several studies have demonstrated a beneficial role for alkali therapy on the progression of CKD [5, 7, 11–15], no data is available if alkali treatment may also allow to better preserve renal allograft function in kidney transplant recipients with metabolic acidosis.

The Preserve-Transplant Study is the first investigator-initiated prospective clinical trial that aims to test whether alkali treatment will help preserving kidney graft function and diminish the progression of chronic kidney disease in renal transplant patients. Thereby, alkali therapy may have the potential to become the first evidence-based adjuvant therapy for the preservation of graft function in kidney transplant patients.

Consequently, the results of the PTS may provide evidence to adapt current recommendations and guidelines for the routine treatment of KTRs suffering from metabolic acidosis. The increasing demand for donor organs worldwide calls for solutions to help to prolong graft survival. The implementation of alkali therapy into the drug regimen of kidney transplant recipients would have a favorable risk-benefit ratio since alkali supplements are routinely used in CKD patients and represent a well-tolerated, safe and cost-effective treatment.

## Trial status and dissemination

The Preserve-Transplant randomized controlled clinical study has received governance approval and is registered at ClinicalTrials.gov (NCT03102996). The trial started recruitment in June, 2017. The study will end in June 2021. First results from this trial are expected in the first quarter of 2022. Publications will be submitted to peer-reviewed journals and the results will be presented at national and international scientific conferences.

## Abbreviations

AE: Adverse event
CKD: Chronic kidney disease
eGFR: Estimated Glomerular Filtration Rate
ESRD: End stage renal disease
GCP: Good clinical practice
KTRs: Kidney transplant recipients
KTx: Kidney transplantation
MA: Metabolic acidosis
PTS: Preserve-Transplant Study
SAE: Serious adverse event
